### Assessments and outcomes

Assessments for both iTAB-CV + SM and SM alone will include evaluation of medication treatment adherence, psychiatric symptoms, health status, self-efficacy for medication taking behavior, illness beliefs, medication attitudes, and habit strength for medication taking behavior. One-on-one assessments will be conducted at 5 time points over a 12-month time period. Adherence and BP will be measured at each of the 5 one-on-one assessments. There will be 3 additional remote/phone assessments which will collect adherence and BP data only. Individuals who drop out of the intervention, and who agree, will be followed up with outcomes assessments over the same 12-month time period that they would have been evaluated had they remained in the study.

Table 2 shows the variable constructs, how they will be measured, mode of data collection, and time points, following the structure of a SPIRIT figure. Demographic and clinical variables measured at baseline will include age, sex, race/ethnicity, education, marital status, and health status. Assessment visits include one-on-one screening, baseline (2 months), V1 (3 months; by phone), V2 (4 months), V3 (5 months; by phone), V4 (6 months), V5 (9 months; by phone), and V6 (12 months). All assessments will be done by a RA trained by the PIs with pre-established and documented reliability standards. Training will use video clips of non-study volunteers or actors. It is expected that patient assessment will require approximately 90 min for the screening assessment and approximately 60 min for the follow-up assessments. Study visits designated as one-on-one may take place in person, via phone or via video conferencing as needed.

**Table 2 Tab2:** Study instruments and assessments schedule

Construct	Measurement	Mode	Screen	BL	V1 phone	V2	V3 phone	V4	V5 phone	V6

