**Secondary outcomes**										
Mood stabilizer adherence	TRQ	REDCap	X	X	X	X	X	X	X	X
Psychiatric symptoms	BPRS	REDCap		X		X		X		X
	MADRS	REDCap	X	X		X		X		X
Self-efficacy for medication taking	MASES-R	REDCap		X		X		X		X
Medication attitudes	BMQ	REDCap		X		X		X		X
	AMSQ	REDCap		X		X		X		X
Habit strength	SRHI	REDCap		X		X		X		X

*BL* baseline

V1 = 3 months

V2 = 4 months

V3 = 5 months

V4 = 6 months

V5 = 9 months

V6 = 12 months

The primary outcomes are SBP and adherence with antihypertensive medication. While SBP is the primary outcome for this analysis, both SBP and diastolic BP will be measured. A recently published joint Policy Statement from the AHA and American Medical Association recommend home-based BP monitoring for the most accurate assessment to minimize biased/artifact findings and yield the most valid results [51]. The joint statement states, “BP may differ considerably when measured in the office and when measured outside of the office setting, and higher out-of-office BP is associated with increased CV risk independent of office BP. Self-measured BP monitoring, the measurement of BP by an individual outside of the office at home, is a validated approach for out-of-office BP measurement. Several national and international HTN guidelines endorse self-measured BP monitoring.” In addition to optimizing accuracy, use of home-based BP evaluation will minimize potential COVID-19 exposure for study participants, most of whom are adults with multiple chronic health conditions.

At screening, participants will be trained on the use of the BP monitor following the BHS protocol [40]. Participants will be asked to take their own BP 2 times consecutively with 1 minute in between each reading and after sitting in a chair quietly for 5 min. BP readings will be collected twice a day, in the morning and evening, for 3 to 7 days while a member of the study staff observes the participant over a video platform, in person, or over the phone. Alternately, the participant can send a screen shot of the BP readings via text to study staff. Once they have obtained 12 readings total (6 in the AM and 6 in the PM), SBP will be averaged across all readings. Participants will also use these procedures to ascertain BP readings at follow-up time points. The interim BP readings will be conducted in real-time using the remote platform or by phone in real time, or if needed, will be measured beforehand and reported during the visit.

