### Secondary outcome measures

Bipolar medication adherence will also be collected using the TRQ for medication targeting mood symptoms including lithium, anticonvulsants, antipsychotics, and antidepressants [58]. Psychiatric symptoms will be assessed using the Brief Psychiatric Rating Scale (BPRS) [59], a clinician rated measure that evaluates the spectrum of symptoms seen in individuals with BD including mania, psychosis, depression, and disorganization. The Montgomery-Asberg Depression Rating Scales (MADRS) [60], a well-validated clinician rated measure, will also be used to measure symptoms of depression and suicidality.

Researchers will utilize self-report questionnaires comprised of the Medication Adherence Self-Efficacy Scale (MASES-R) [61], the Self-Report Habit Index (SRHI) [62], the Beliefs about Medicines Questionnaire (BMQ) [63], and the Attitudes toward Mood Stabilizers Questionnaire (AMSQ) [64] to capture possible moderators and mediators to medication adherence. Dose of intervention (frequency of texts) and engagement (% texts answered) will be collected from the iTAB-CV system. Intervention acceptability/satisfaction will be assessed via questionnaire as well as open-ended process measures regarding ease of use of the system and how it can be improved. Healthcare utilization will also be measured via self-report questionnaire.

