### Data analysis plan

For the primary intent-to-treat analyses (aims 1 and 2), linear mixed effects longitudinal analysis of adherence (TRQ past month is primary) and SBP to 4 months (V2) will be conducted. A treatment variable will be included to indicate randomization to either iTAB-CV + SM or SM alone. Secondarily, we will also consider models with longer-term outcomes. Within the longitudinal models, significant interaction of the treatment variable with time indicates that the treatments have a different course of response. The researchers will first fit models with time as a covariate and, alternatively, consider time period as a categorical variable. Time by treatment interaction will be of primary inferential interest. To account for possible imbalances across treatment groups and other sources of variation, explanatory variables such as gender, ethnicity, and BD diagnosis type (I vs. II) will be considered for inclusion in the mixed models.

Researchers will consider representing TRQ scores as binary outcomes, indicating whether or not an adherence threshold has been met (e.g., 80% adherent). Researchers will thus also consider generalized linear mixed models for binary outcomes (SAS PROC GLIMMIX), as well as fitting a longitudinal model on the difference values with baseline value adjustment. Graphical methods will be used extensively to examine distributions of residuals, identify potentially influential points, and guide data transformations to better approximate normality if warranted. Sensitivity analysis of results will be conducted by modeling a range of plausible correlation structures.

In secondary analyses for both aims 1 and 2, follow-up at 6 and 12 months (V4 to V6) will also be compared in the respective longitudinal analyses for adherence and SBP. The researchers will conduct contrast analyses of treatment by (discrete) time interaction at time periods V4 and V6 and differences from baseline in treatment dose-level subgroups (higher versus lower booster levels) at V4 and V6 using two sample *t*-tests or nonparametric Mann-Whitney tests. Additionally, the researchers will compare corresponding TRQ and eCAP™ adherence levels. Correlation between the measures will be estimated and Bland-Altman plots will be generated [67].

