The researchers will model secondary outcomes over time in a similar manner as in aims 1–2 through longitudinal mixed models when appropriate. The researchers will consider generalized linear models when distributions of outcomes are not approximately normally distributed or transformations of outcome variables to normality. The researchers will also conduct exploratory moderator analyses of the explanatory variables in the primary mixed models for adherence and SBP. Moderators to be explored include depression, psychiatric symptoms, age, sex, engagement, medication attitudes, self-efficacy, and BD type I vs. II for each of the primary outcome models. For moderator analyses, in an exploratory manner, the researchers will consider the addition of interaction effects with treatment and time for each potential moderator.

For aim 3, habit strength scores will be analyzed as an outcome in a similar manner as in aim 1. The researchers will assess dose (frequency of texts), depression, engagement, medication attitudes, and self-efficacy as moderators of habit strength. The researchers will also consider habit strength as a mediator for improved longer-term adherence at 4, 6, and 12 months. The researchers will conduct mediation analyses using approaches described by MacKinnon [68] and Preacher and Hayes [69]. These analyses will involve the treatment variable and change in adherence values. Bootstrapping methods will be used to assess indirect effects, as in Preacher and Hayes [69]. The research team will also consider, as needed, use of generalized linear models through a mediation formula approach [70, 71] to estimate the direct effect of the treatment and indirect effects through the proposed mediator.

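### The 4-month mediation cannot show whether habit or adherence comes first, and engagement and text dose are not moderators of the treatment effect

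*Protocol article*

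**What the plan says.** **Mediation.** The Data analysis plan says: "The researchers will also consider habit strength as a mediator for improved longer-term adherence at 4, 6, and 12 months". On the variables it adds: "These analyses will involve the treatment variable and change in adherence values". It does not name the SRHI visit that serves as mediator for each outcome. In Table 2 the row "Habit strength" is marked at baseline, V2, V4 and V6, and at none of the phone visits. Baseline is month 2, V2 month 4, V4 month 6 and V6 month 12. The section on the educational video places the baseline assessments before randomisation.

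**Adherence measure.** The primary models are described as "linear mixed effects longitudinal analysis of adherence (TRQ past month is primary) and SBP to 4 months (V2) will be conducted".

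**Moderators.** For the primary outcome models: "Moderators to be explored include depression, psychiatric symptoms, age, sex, engagement, medication attitudes, self-efficacy, and BD type I vs. II". For habit strength: "The researchers will assess dose (frequency of texts), depression, engagement, medication attitudes, and self-efficacy as moderators of habit strength". Objectives also lists text frequency and engagement as moderators of the 6-month outcome. Secondary outcome measures gives their source: "Dose of intervention (frequency of texts) and engagement (% texts answered) will be collected from the iTAB-CV system". Each moderator would enter through interactions with treatment and time.

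**Text streams.** Under Intervention, iTAB-CV participants get one adherence text a day for two months, then a weekly or tapering booster according to the second randomisation. Both arms get weekly mood texts and monthly refill reminders. The self-monitoring (SM) arm gets no adherence texts.

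**The concern.** A mediation analysis needs the mediator to act before the outcome, and a moderator has to be something that treatment cannot alter. Three of the stated analyses miss one of these conditions.

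- At 4 months, habit is scored at the end of the period over which adherence is recalled.
- Engagement has no value before randomisation and means something different in each arm.
- Text dose is part of the assigned treatment.

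Habit formation is the theory on which the article rests the intervention, and Objectives says that the moderator findings will guide how content and frequency are matched to patients. A 4-month indirect effect that really reflects adherence building habit, or an engagement interaction that compares unlike quantities, would feed into that tailoring.

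**Working it through.** The article gives no figure for these analyses, so there is none to reproduce. The check sets the schedule against the recall windows, then looks at the size of the problem and at the design columns.

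**1. Time order** (Table 2 visits; past-month TRQ)

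| Outcome visit | TRQ window (months) | Post-randomisation SRHI at or before the window opens |
|---|---|---|
| V2 | 3 to 4 | none |
| V4 | 5 to 6 | V2 |
| V6 | 11 to 12 | V2, V4 |

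Baseline SRHI precedes randomisation and so cannot carry a treatment effect. V1 has no SRHI. The past-week TRQ does not help, because it also closes at the V2 visit.

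**2. Size of a false indirect effect**

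Inputs from Sample size calculations: between-arm difference 16.1, AR(1) correlation 0.44, error variance 308 (SD = √308 = 17.55), and 200 × (1 − 0.25) = 150 participants. Assumptions: the correlation of 0.44 applies from baseline to V2 and from V2 to V4; the 16.1 difference persists to V4; V2 habit depends only on V2 adherence, with within-arm correlation r of 0.2, 0.3 or 0.5; and habit has no effect on adherence. The article gives no value for r.

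With adjustment for baseline adherence, the conditional variance factor is 1 − 0.44² = 0.8064, and:

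- treatment to habit: a = r × 16.1 / 17.55
- habit to V2 adherence: b = r × 17.55 × 0.8064 / (1 − 0.1936 r²)
- spurious share of the effect: ab / 16.1 = 0.8064 r² / (1 − 0.1936 r²)

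This gives:

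- r = 0.2: 0.0323 / 0.9923 = 3%
- r = 0.3: 0.0726 / 0.9826 = 7%
- r = 0.5: 0.2016 / 0.9516 = 21%

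A simulation of 2000 runs per value of r gave the same shares. Counting an indirect effect as significant when both paths had |z| > 1.96, the false-positive proportions were:

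| Model | r = 0.2 | r = 0.3 | r = 0.5 |
|---|---|---|---|
| V2 habit, V2 adherence | 11% | 37% | 80% |
| V2 habit, V4 adherence, baseline adherence adjusted | 2% | 10% | 49% |
| As above, also adjusted for V2 adherence | 1% | 2% | 4% |

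Lagging the outcome is not enough by itself; adjustment for V2 adherence is also needed.

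**3. Engagement**

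To V2, counting each prompt once, a week in iTAB-CV holds 7 adherence texts plus 1 mood text, 8 in all. A week in SM holds 1 mood text. The share answered therefore has different content and a different denominator by arm. Under Intervention, three consecutive days of missed messages trigger a staff call, so low engagement also changes the contact received.

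**4. Dose**

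Let T = 1 for iTAB-CV and 0 for SM, and let A be the assigned adherence-text frequency, with A = 0 whenever T = 0. Then T × A = A at every visit, so the interaction column equals the dose column. If the texts common to both arms (frequency w) are counted, D = w + A and T × D = D − w + wT, which is an exact linear combination of the intercept, D and T. To V2, A is also constant within iTAB-CV. Afterwards it varies only through the booster. The interaction cannot be separately estimated in either period.

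**The case against.** The strongest reply is that these analyses are secondary or exploratory, and that no primary estimate, alpha level or sample size depends on them. That stands, and it limits the weight of the point.

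Four wider readings are tempting, and the document does not support them.

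- *Habit strength is unsuitable because it arises after randomisation.* A mediator must do so. This is no fault.
- *The order at month 4 is reversed, so the mechanism question cannot be answered.* SRHI and TRQ are taken at the same V2 visit, and no mediator visit follows its outcome visit. The order there is unresolved rather than reversed, and two of the three time points can be ordered.
- *The moderator list as a whole is post-randomisation.* Of the eight moderators for the primary outcomes, age, sex and BD type are fixed. Depression, psychiatric symptoms, attitudes and self-efficacy have baseline scores, and nothing says that later values will be used. Only engagement necessarily arises after randomisation.
- *An engagement interaction would mostly show that adherent people answer texts.* A reply that the medicine was not taken also counts as an answer, so this cannot be asserted.

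On dose, it can fairly be said that Objectives places it at 6 months, after the booster randomisation, and that dose is absent from the moderator list for the primary outcome models. Constancy between months 2 and 4 is therefore not the decisive argument. The collinearity remains at 6 months because SM receives no adherence texts. The booster comparison is a sound randomised contrast, but it is not moderation of iTAB-CV against SM.

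The SRHI visit for each model could be left to a fuller plan. For month 4, however, no choice of visit supplies a post-randomisation score before the outcome window.

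**Conclusion.** The point holds for three specific analyses.

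- **4-month mediation:** associational only. This follows from the schedule and needs no numerical assumption. The false-positive range of 11% to 80% rests on the assumed correlations and on baseline-adjusted adherence standing in for the change values that the plan mentions.
- **Engagement:** its interaction with treatment is not effect moderation.
- **Dose:** its interaction with treatment is not separately estimable. This takes dose as the assigned frequency. If delivered frequency were meant, any further variation would itself arise after randomisation, as engagement does.

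The 6- and 12-month mediation remains feasible, subject to no unmeasured confounding of habit and adherence. The primary analyses are untouched. The change is worth making because the results are intended to shape later versions of the intervention.

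**What to change.** In the Data analysis plan, and for the moderators also in Objectives:

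1. Name V2 SRHI as the mediator of V4 and V6 adherence, adjusted for baseline habit, baseline adherence, V2 adherence, and booster assignment within iTAB-CV.
2. Label the 4-month habit analysis as associational, or drop it.
3. State that depression, psychiatric symptoms, medication attitudes and self-efficacy enter as moderators at their baseline values.
4. Remove engagement and dose from the treatment-moderator lists. Report engagement descriptively within iTAB-CV, and address dose through the high-versus-low booster contrast already planned at V4 and V6.

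The cost is wording and one exploratory mediation time point; no new data are needed. Adjusting for V2 adherence may also remove part of a true habit effect that acted through adherence before V2, so the lagged estimate may understate mediation. The report should say so.

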### Sample size calculations

Power analyses are based on computations from the Repeated Measures and Sample Size (RMASS) [72] with inputs estimated from prior study data. Our projected sample size is *n* = 200, with 100 participants per arm. In this power analysis, the research team will assume type I error levels of 0.025 for each of the two primary analyses, using Bonferroni correction to account for multiple comparisons. Conservatively, for this study, the researchers will assume 25% attrition based on a previous 12 month trial conducted by members of the study team with individuals with comorbid serious mental illness and diabetes [73]. For sample size requirement for aim 1, the investigators used past-month TRQ as an approximation of expected and longer-term maintenance adherence status and considered primary outcomes to be at 3 months. The investigators expect similar or even greater effect sizes at 4 months given the longer treatment duration. In the pilot study, there was 23.10% improvement in TRQ observed for iTAB-CV. The control comparator for the efficacy trial will be SM of adherence, BP, and mood. Based on the literature, no improvement in self-reported adherence was reported in a similar control arm [74]. The study staff thus assume no change in adherence. In a BD adherence RCT, 7% improvement was observed in the control arm. Hence, the investigators conservatively project a 7% mean improvement in adherence among controls. Thus, (1) there is a mean difference of 16.1% in adherence after 4 months between arms and (2) suppose autoregressive (AR(1)) model covariance structure with correlation coefficient of 0.44 and an error variance of 308, as estimated value from the data. With assumed attrition of 25%, for a 2-sided test of the treatment by time interaction effect being equal to zero, and with alpha = 0.025 and power = 0.80, the required total sample size is approximately 78.

From the pilot data, mean screen SBP was 144.81 (SD 15.46). Change from screen to 3 months with the iTAB-CV intervention saw a mean reduction in SBP of 8.78. Reductions in BP of at least 2 mmHg can significantly reduce the incidence of cardiovascular disease and its complications in both hypertensive and normotensive individuals, and reductions of the magnitude seen in this team’s pilot work is well above thresholds that are considered clinically meaningful [75]. Based on our preliminary mixed model, the researchers also observed compound symmetry correlation parameter value of 0.36. This covariance model had similar model fit as with an AR(1) model in terms of AIC/BIC criteria and parameter estimate values. The researchers will assume no SBP pressure change is observed in the SM arm and estimated error standard deviation of 15.46, as observed [38]. Finally, in a linear mixed model with participant-level random effects, with two-sided type I error of 0.025, power = 0.80 for the projected sample size of 182 participants. The study staff will target a sample of 200 for the study to allow for some deviation from assumptions. Thus, the researchers should have sufficient statistical power for the first 2 primary aims.

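### Bonferroni at 0.025 is the only multiplicity rule stated for the two primary outcomes; Holm keeps the same family-wise error and would raise SBP power from about 0.84 to 0.90 at N = 200

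*Protocol article*

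**What the plan says.** The Sample size calculations section says that the team will "assume type I error levels of 0.025 for each of the two primary analyses, using Bonferroni correction to account for multiple comparisons". The sentence opens by limiting itself to the power analysis.

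The same section sizes each outcome at that level:

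- **Adherence (TRQ, past month):** about 78 participants in total for power 0.80 at alpha 0.025, with 25% attrition.
- **SBP:** "with two-sided type I error of 0.025, power = 0.80 for the projected sample size of 182 participants".

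The trial will then "target a sample of 200 for the study to allow for some deviation from assumptions", "with 100 participants per arm".

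The Data analysis plan section defines the primary models (linear mixed models to month 4, with the treatment-by-time interaction of main interest). It gives no significance level and no step-down, hierarchical or alpha-recycling rule. Bonferroni is therefore the only multiplicity method that the article names.

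**The concern.** The two primary outcomes are sized very unequally: SBP needs more than twice as many participants as adherence. When one of two tests is almost sure to succeed, a fixed half-and-half split of alpha leaves the harder test at 0.025 although the family-wise requirement no longer demands it. Holm's procedure uses that slack. The smaller p-value is compared with 0.025 and, if it is rejected, the other is compared with 0.05.

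At stake is the chance of detecting an SBP effect of the planned size. SBP has the smaller power margin of the two outcomes, and the step from 182 to 200 is the plan's only stated allowance for assumptions that turn out too favourable.

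**Working it through.** **Inputs, all from Sample size calculations.** SBP: "Change from screen to 3 months with the iTAB-CV intervention saw a mean reduction in SBP of 8.78"; for control, "The researchers will assume no SBP pressure change is observed in the SM arm"; "estimated error standard deviation of 15.46"; compound-symmetry correlation 0.36; two-sided alpha 0.025; power 0.80; N = 182. Adherence: N of about 78 at the same alpha and power. Attrition 25%. Target N = 200, 1:1.

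**Step 1: reproduce the plan's 182.** I assumed three equally spaced visits (baseline, months 3 and 4), a linear treatment-by-time contrast estimated by generalised least squares, and dropout rising linearly to 25% at the last visit.

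- Without dropout, the SD of the baseline-to-month-4 contrast is 15.46 × √(2 × (1 − 0.36)) = 17.49.
- With that dropout pattern it becomes 19.24.
- N = 4 × 19.24² × (2.241 + 0.842)² / 8.78² = 182.5.

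This agrees with the stated 182, so attrition is already inside that figure.

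**Step 2: noncentrality and power at a given N.** Since 182 gives power 0.80 at two-sided 0.025, the SBP noncentrality at N is (2.241 + 0.842) × √(N/182). For adherence, replace 182 by 78.

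- SBP at N = 200: 3.083 × √(200/182) = 3.232. Power is 0.839 at alpha 0.025 and 0.898 at alpha 0.05.
- Adherence at N = 200: 3.083 × √(200/78) = 4.937. Power at alpha 0.025 is 0.996.

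**Step 3: SBP power under Holm.**

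Power = P(p_SBP ≤ 0.025) + P(0.025 < p_SBP ≤ 0.05 and p_TRQ ≤ 0.025)

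With independent tests at N = 200 this is 0.839 + (0.898 − 0.839) × 0.996 = 0.898. Test correlations of 0.3 and 0.6 also give 0.898.

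| N | SBP power, Bonferroni | SBP power, Holm |
|---|---|---|
| 182 | 0.800 | 0.869 |
| 200 | 0.839 | 0.898 |

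A cruder reading, with 150 completers out of 200 and a simple change score, gives 0.80 and 0.87, so the gain is again about 7 points.

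**Step 4: dependence on the adherence result (N = 200).** The adherence effect is scaled down and SBP kept as planned. Bonferroni stays at 0.839 throughout.

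| Adherence effect, share of assumed | Adherence power at 0.025 | SBP power, Holm |
|---|---|---|
| 100% | 0.996 | 0.898 |
| 75% | 0.928 | 0.894 |
| 50% | 0.590 | 0.874 |
| 25% | 0.157 | 0.848 |
| 0% | 0.025 | 0.840 |

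**Step 5: sensitivity to the figure of 78.** I could not reproduce 78 closely: linear dropout with AR(1) gave about 63 with two visits and 86 with three. This matters little. If adherence needed 116, its power at N = 200 would be about 0.96 and Holm SBP power about 0.896.

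**Step 6: error control.** If both null hypotheses are true, the two procedures have the same family-wise error, because each makes an error only when at least one p-value is at or below 0.025: 1 − 0.975² = 0.0494 for independent tests.

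**The case against.** The strongest reply is that nothing here is an error. Bonferroni is valid, it is applied consistently to both outcomes, and both required sizes lie below 200. That stands, and the point is one of efficiency only.

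A second reply is that the quoted sentence does not fix the final test. A reader might infer that both outcomes will be tested at 0.025 whatever the other shows. The documents do not say so: 0.025 is an assumption for sizing, and sizing at 0.025 is compatible with Holm at analysis, because Holm's first step uses that level. A separate analysis plan may already name Holm, which would settle the matter. Until then, the only method on record is the less powerful one.

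A third reply is that Holm is not wholly free. If adherence truly improves and SBP does not, the SBP false-positive rate rises from 0.025 towards 0.05, still within the family-wise bound. The adherence test that would usually release the extra alpha is a self-report from participants who know their arm, so reporting bias could relax the SBP threshold, whereas a fixed split keeps that threshold independent of TRQ. That is a fair consideration. Even so, Holm loses no rejection that Bonferroni would make. Exactly matching simultaneous intervals are also less simple under Holm.

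Finally, the gain depends on adherence. With no adherence effect, Holm adds almost nothing (0.840 against 0.839).

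**Conclusion.** The point holds as an efficiency improvement. On the plan's own inputs, Holm adds about 6 points of SBP power at N = 200 (0.84 to 0.90) and about 7 at N = 182 (0.80 to 0.87). At N = 200 the SBP type II error falls from about 16% to about 10%. The size of the gain rests on the planned SBP and adherence effects, on the stated sample sizes of 182 and about 78, and on the normal approximation. That it cannot be negative rests on none of these.

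Two stronger readings are tempting and should not be drawn. One is that SBP is underpowered or its stated power wrong; the plan's 0.80 at 182 reproduces. The other is that SBP deserves the recovered alpha because it is the more important outcome; the article lists SBP and adherence as joint primary outcomes and ranks neither. The recommendation needs no ranking, since Holm treats the two alike.

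**What to change.** Before unblinding, add to the Data analysis plan section that the two primary tests use Holm's procedure at a two-sided family-wise level of 0.05: the smaller p-value is compared with 0.025 and, only if it is rejected, the larger with 0.05. Leave the sample size and its 0.025 assumption as they are. If simultaneous intervals are wanted, report 97.5% intervals for both outcomes and note that they may not match the Holm decision exactly for the second test.

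The cost is a sentence or two of text. Recruitment, visits and data collection do not change. What is given up is the exact match between intervals and tests, and the stricter 0.025 limit on an SBP false positive when adherence truly improves.
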